#### Sample size of cases

The sample size of 4100 study participants anticipated in the intervention arm (Ife North LGA) will include both asymptomatic (40–70 years) and symptomatic (30–70 years) women that will undergo screening and diagnostic evaluations respectively. In any screening exercise, there will be symptomatic cases that will use the opportunity of screening to present for evaluation. We anticipate a CDR of at least 3.5%. This expectation is supported by our previous publication of a mixed screening and diagnostic population in this geographic region demonstrating a breast CDR of 3.5% [19]. The CDR in this study will be the number of cancers detected among all study participants, including both the symptomatic and screening arms.

Our previous data demonstrate that the mean breast tumor size from an entirely symptomatic population at OAUTHC was 10.5 cm. This is much larger than findings from our recent study from the same region which included a screening population which demonstrated an average breast cancer size of 3.3 cm [19, 22]. We therefore project that cancers in the intervention community will be follow a similar pattern.

The primary outcome measure in this study is the stage at diagnosis. To achieve this, we projected the number of cases needed to detect a difference in the proportion of cases based on stage at diagnosis between the two study arms. From our preliminary data of 25 staged cancers, there were 7 (7/12, 58.3%) and 2 (2/13, 15.38%) stage IV cancers in the control and intervention arms respectively, with a 43% difference between the two groups. In order to detect a 43% difference in stage IV diagnoses between the two study arms with 80% statistical power at an alpha of 0.05, 23 cases will be needed in each arm. Our preliminary data show 13 total cancer cases detected in 791 patients and 12 total cancer cases detected in 82 patients in the intervention and control arms, respectively, in the first year. Going by this annual accrual rate, in two years, there should be 26 cancer cases out of 1582 patients in the intervention arm and 24 cancer cases out of 164 patients in the control arm. Therefore, achieving the 23 cases required for statistical significance in the stage at diagnosis in each arm at the end of the 2-year study period is possible.

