#### Control arm

The control LGA is about 4 kilometers from OAUTHC which is the referral tertiary hospital in this study. There are radiological (including ultrasound, mammography, computerized tomography, and magnetic resonance imaging services), pathological and surgical specialty services for breast cancer within OAUTHC which is also the primary institution of the study’s principal and co-investigators in Nigeria. In the control LGA, awareness creation will follow a similar procedure as outlined above for the intervention LGA. No other intervention will take place in the control arm. Women will not be invited to participate in a screening program and there is no community-based imaging, biopsy, or navigation. Women are expected to present to the PHCs if they have breast complaints which is a routine practice. Management of patients with breast-related complaints will be based on the current standard of care which is a review by the CHNs who refer or clinically manage otherwise based on his/her assessment. Twice a month, research staff will visit the selected PHCs in the control LGA to obtain data on the number and records of breast-related cases seen at the PHCs and those referred to OAUTHC. Patients referred to OAUTHC for suspicion of breast cancer will be tracked to determine the stage at diagnosis and the timelines from presentation at the PHC to eventual treatment at OAUTHC. In addition, patients presenting directly to OAUTHC from the LGA based on self-referral will also be identified and their data obtained.

Although the control arm participants do not have intervention provided in their LGA, they however get same workup, management and are navigated along the same pathway as the intervention arm participants once they present in OAUTHC for screening and diagnostic evaluation.

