### Statistical analyses

All data entered into the REDCap database will be exported as a dataset into R 4.2. Sociodemographic characteristics of the participants will be assessed using medians and interquartile ranges (IQR) for continuous variables and counts and percentages for categorical variables. Participation rate, retention rate, abnormal call rate, rate of late-stage diagnosis, and CDR will be reported as proportions with 95% exact confidence intervals. As for late-stage diagnosis, stage 4 cancers will be considered late-stage. The above-mentioned metrics will be compared between the intervention and control arms using Chi-square tests or Fisher’s exact test. The time intervals from presentation to treatment will be reported using medians and IQR and will be compared between the intervention and control arms using the Wilcoxon rank-sum test. The rate of late-stage diagnosis will be estimated and compared between the intervention and control arms on a yearly basis, starting from baseline, to assess if the intervention arm shows betterment in this rate consistently. Bonferroni correction for type I error will be implemented (α* = 0.0167) for this comparison. A logistic regression analysis which accounts for the ward (random effect) in which the patient was examined will also be performed with late-stage diagnosis as the dependent variable and time of screening, the interaction between the allocated groups (intervention and control arms), and time of screening as the independent variables. For all statistical comparisons (other than the one mentioned immediately above), the type I error rate (α) will be set to 0.05. All statistical analyses will be conducted using R 4.2 software [24]. Sample size calculations were done using the clinfun package of the R 4.2 software [25].

We do not anticipate any missing data due to loss of follow-up because the research team will make every effort to retain recruited participants. However, if missing data issues do arise, we will implement multiple imputation techniques, which impute missing data under the missing at random (MAR) assumption. Sensitivity analysis of the findings after multiple imputations will thereby be performed and these findings will be compared to those obtained from complete case analyses.

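### The supplementary logistic model for stage IV diagnosis lists time and arm-by-time but not arm, so with numeric time a constant gap between the two LGAs is partly reported as a difference in trend

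*Protocol article*

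**What the plan says.** Under Sample size of cases, the article states: "The primary outcome measure in this study is the stage at diagnosis". Under Statistical analyses, "stage 4 cancers will be considered late-stage", and late-stage rates are compared between arms by chi-square or Fisher's exact test, with yearly comparisons from baseline at a Bonferroni level of 0.0167.

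A regression is then added to those tests: "A logistic regression analysis which accounts for the ward (random effect) in which the patient was examined". Its outcome is whether a case is stage IV, and its predictors are listed thus: "time of screening, the interaction between the allocated groups (intervention and control arms), and time of screening as the independent variables". Time of screening has its own place in the list, and so does the interaction. Allocated group does not.

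Three other parts of the article bear on this:

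- **Study design and setting:** each arm is one LGA. The control LGA is about 4 km from the referral hospital (OAUTHC) and the intervention LGA about 25 km.
- **Program evaluation and outcome measures:** late-stage disease is expected to start high and then fall in the intervention arm, and the yearly estimates are meant to show a difference between arms in annual trend.
- **Control arm:** "patients presenting directly to OAUTHC from the LGA based on self-referral will also be identified and their data obtained".

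**The concern.** An arm-by-time slope without an arm term makes the fixed part of the model start both arms at the same odds of stage IV disease. Randomising many units could justify that. One LGA per arm cannot, and the two LGAs differ in distance to the hospital. A level difference that is constant from the first day then has to be expressed through the slope or the ward intercepts.

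The slope is the only arm-related coefficient in the only regression planned, and it corresponds to what the article wants to learn: whether the arms diverge over time. A constant LGA difference could be read as a programme effect that grows, or as harm that grows. An immediate and sustained programme effect would likewise be described as a trend.

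Two inputs are also loosely fixed. Ward is the one in which the patient was examined, yet self-referred control cases are examined at OAUTHC, which lies in a third LGA. The date that counts as time of screening for a symptomatic control case is not stated.

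**Working it through.** **1. The plan's own figures.** Sample size of cases reports that "there were 7 (7/12, 58.3%) and 2 (2/13, 15.38%) stage IV cancers in the control and intervention arms respectively" and that "with 80% statistical power at an alpha of 0.05, 23 cases will be needed in each arm". Sidedness is not stated; I assume two-sided. With p1 = 0.58, p2 = 0.15, d = 0.43 and mean 0.365:

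- Uncorrected: n = [1.96 √(2 × 0.365 × 0.635) + 0.842 √(0.58 × 0.42 + 0.15 × 0.85)]² / 0.43² = (1.334 + 0.513)² / 0.1849 ≈ 18.5, so 19.
- Continuity-corrected: (18.5 / 4) × [1 + √(1 + 4 / (18.5 × 0.43))]² ≈ 22.9, so 23. This reproduces the article's figure.
- 0.05 / 3 = 0.0167, which reproduces the Bonferroni level.

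The sample size therefore rests on two proportions, not on the regression. The projected cases at two years are 26 intervention and 24 control.

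**2. What the listed terms can express.** With numeric time t and arm A (0 control, 1 intervention), the fixed part is

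logit P(stage IV) = b0 + b1 t + b2 (A × t).

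At t = 0 this is b0 in both arms. Take a constant gap of 58.3% v 15.4% as an example: the log-odds are ln(7/5) = 0.336 and ln(2/11) = −1.705, a difference of −2.04 at every t. There is no fixed term for that difference.

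**3. Large-sample coefficient, ward left out.** Time is continuous over 0–2 years and nothing truly changes over time.

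| Assumed constant rate, control v intervention | b2 per year, listed terms | Odds ratio per year | b2 with arm added |
|---|---|---|---|
| 58.3% v 15.4% | −1.56 | 0.21 | 0.00 |
| 50% v 30% | −0.63 | 0.54 | 0.00 |
| 15% v 35% | +0.83 | 2.30 | 0.00 |

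In the first row, adding arm moves the whole gap to the arm term (−2.04).

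**4. False interactions at the planned size.** Simulated trials had 24 control and 26 intervention cases, entry uniform over two years, and likelihood-ratio tests of arm x time at 0.05. The ward version has a random intercept over 5 wards (3 intervention, 2 control). Where two figures appear, they come from two separate sets of simulations; the set giving 53% and 20% used 250 trials per scenario.

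| Assumed constant rate, control v intervention | Listed terms, no ward | Listed terms, ward intercept |
|---|---|---|
| 58.3% v 15.4% | 82% | 53%, 49% |
| 50% v 30% | 26% | 20%, 18% |
| 15% v 35% | 33% | 24% |
| 40% v 40% | 6% | not run |

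With arm added and ward fitted, the rate is 6–8%; the small excess over 5% is the small-sample behaviour of the test. For 58.3% v 15.4% with ward fitted, the median false slope is still −1.65 per year.

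**5. Ten times the cases, ward fitted (80 trials, 58.3% v 15.4%).** The median false slope is about 0, but rejection is 19%, against 7.5% with arm. The ward intercepts can take up the gap when data are plentiful. About 50 cases are not enough.

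**6. Categorical time.** If time is a set of periods and arm-by-time is fitted at every level including baseline, the listed terms re-express the full model: one arm contrast per period and no equal-baseline constraint. Those coefficients are level differences within a period and should not be read as changes over time.

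**The case against.** The strongest objection is that the planned model contains a ward random intercept. Wards are nested in arm, so the intercepts can carry a level difference between LGAs. This stands in part. A reader might infer from the fixed terms alone that the model forces equal odds at time zero. It does not; it shrinks the gap without excluding it. For the same reason the 82% obtained without ward should not be quoted for this plan. The ward-inclusive rates are lower but remain far above those with arm included.

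The second objection is that time may be categorical. The yearly comparison from baseline, with 0.05 split three ways, fits that reading. The coding is not stated, and under categorical coding the concern falls away.

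Third, the wording is awkward, with time of screening named twice, and may be shorthand for a full arm-by-time specification. That is possible, but the printed list omits arm.

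Fourth, the 58.3% v 15.4% gap was observed in the first year under the programme and is the difference the trial is sized to detect. It is no evidence of a pre-existing gap and serves here only as an illustrative size. A reader might also infer that the omission favours the intervention. The article does not support that. The control LGA is the one nearer the hospital, and a gap in that direction (15% v 35%) produces apparent harm.

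Fifth, a reader might conclude that time of screening does not exist for controls. The article describes screening and diagnostic groups in both arms, and controls who present at OAUTHC for screening and diagnostic evaluation. What can be said is that the date to use is not fixed for symptomatic control cases, and that self-referred cases have no study ward of examination.

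**Conclusion.** Wrong as written, in a supplementary model. If time is numeric, the listed terms let a constant LGA difference, or an immediate programme effect, appear partly as a difference in trend. With 24 + 26 cases, the ward intercept fitted and no true change over time, the interaction is falsely significant in roughly 50%, about 20% or about 24% of trials for assumed gaps of 58.3% v 15.4%, 50% v 30% and 15% v 35%, against 6–8% with arm included. With no gap (checked without the ward intercept) there is no inflation.

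These figures rest on numeric time, uniform entry, five wards, and gap sizes and directions that are assumptions, since no pre-intervention stage distribution by LGA is given.

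A reader might take this as invalidating the primary comparison. It does not: stage IV rates are also compared by chi-square or Fisher's exact test, and the 23 cases per arm rest on that comparison.

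**What to change.** Specify the model as late stage ~ arm + time + arm x time, with a random intercept for ward. State whether time is numeric or categorical, and define it the same way in both arms, for example as date of diagnosis. Use ward of residence in place of ward of examination, so that self-referred cases seen at OAUTHC have a ward. Report the arm effect and the interaction separately.

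The cost is a sentence or so of text and no new data beyond the residential address, which the Discussion already says will be matched against the LGAs. The interaction will be estimated less precisely, because level and trend are no longer merged. Penalised estimation is an option if cells are sparse, not a requirement.

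The added arm term separates a constant gap from a difference in trend. With one LGA per arm it still cannot separate the intervention from the LGA, and the report should say so.

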A descriptive analysis of the data will be done at 1.5 years for the retention rate and abnormal call rate to inform our decision for future investigations. The rate of late-stage diagnosis will be estimated on a yearly basis. However, no stopping rules will be employed. This estimation will purely serve the purpose of detecting any difference in the annual trends of the stage of diagnosis over time between the intervention and control arms.

The initial findings for the subset of women who undergo a second round of screening will be examined to identify the stage of presentation in this group of women if diagnosed during the second round. Given in our setting ~80% of patients with breast cancer present in stages 3 and 4, we expect to see a trend toward earlier stage of presentation (stages 0, 1 and 2) in women undergoing repeat breast evaluation.

The 2-year study period is enough to generate adequate data to measure the participation rate and difference in stage at diagnosis between the study arms, as elaborated in the sample size calculation of the cancer cases. In addition, this study will provide a groundwork for exploring the difference in CDR between the 2 modalities (CBE and enhanced CBE) and the time to treatment, generating data to guide future studies in our population.

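### The late-stage regression lists time and group-by-time but no term for allocated group; if time is counted from launch, a constant gap between the two LGAs shows up as a difference in trend

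*Protocol article*

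**What the plan says.** Under Statistical analyses, the protocol article defines the outcome: "As for late-stage diagnosis, stage 4 cancers will be considered late-stage". The late-stage rate is among the metrics of which it says: "The above-mentioned metrics will be compared between the intervention and control arms using Chi-square tests or Fisher’s exact test". The same rate is also "compared between the intervention and control arms on a yearly basis, starting from baseline", at a Bonferroni level of 0.0167.

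A model is then added: "A logistic regression analysis which accounts for the ward (random effect) in which the patient was examined will also be performed". Late-stage diagnosis is the dependent variable, with "time of screening, the interaction between the allocated groups (intervention and control arms), and time of screening as the independent variables". Time is named twice and allocated group only inside the interaction. The section does not say whether time is continuous or a yearly category, or where it starts.

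The section Program evaluation and outcome measures gives the aim of the yearly estimation of the late-stage rate as "detecting any difference in the annual trends of the stage of diagnosis over time between the intervention and control arms".

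The planning rates are in Sample size of cases: "there were 7 (7/12, 58.3%) and 2 (2/13, 15.38%) stage IV cancers in the control and intervention arms respectively".

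**The concern.** Taken at its word, the fixed part of the model is intercept + time + arm × time. At time zero the arm term vanishes, so both LGAs must have the same fitted odds of stage IV there. A gap that is present throughout has only two places to go: the interaction coefficient and, in part, the ward intercepts.

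The design gives no assurance of equality at launch. Each arm is a single LGA, about 25 km and 4 km from the referral hospital. Asymptomatic women are invited in one LGA and not in the other, so the mix of cases can differ from the first day.

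At stake is the claim that late-stage disease falls faster under the programme. This regression is the only planned analysis of the primary outcome that uses both time and ward, and the only model with a trend contrast. As listed, it can report a diverging trend where none exists.

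**Working it through.** **Inputs.** Stage IV proportions 7/12 = 58.3% (control) and 2/13 = 15.4% (intervention), from Sample size of cases. Projected cases at two years: 2 × 12 = 24 control and 2 × 13 = 26 intervention, same section. Wards: two control, three intervention.

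**The plan's own figures.** For 58.3% v 15.4%, two-sided Fisher's exact power at 0.05 is 78.6% with 22 cases per arm and 81.4% with 23. The stated 23 per arm is reproduced. So is 0.05/3 = 0.0167.

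**Step 1: large-sample fit to a constant gap.** Hold the two rates fixed at every time. The true log-odds are ln(7/5) = 0.3365 in control and ln(2/11) = −1.7047 in intervention, a difference of −2.0412 (OR 0.13). No trend exists in either arm.

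The listed terms, with continuous time from 0 to 2 years, give

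logit(p) = −0.479 + 0.615·t − 1.586·arm·t.

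| Time | Control, fitted | Intervention, fitted | True |
|---|---|---|---|
| 0 | 38.2% | 38.2% | 58.3% v 15.4% |
| 1 year | 53.4% | 19.0% | 58.3% v 15.4% |
| 2 years | 67.9% | 8.1% | 58.3% v 15.4% |

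The spurious interaction is exp(−1.586) = 0.21 per year. Adding arm returns −2.0412 for arm and 0 for the interaction.

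**Step 2: the result depends on how time is coded.** Same constant gap, listed terms only:

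- Time numeric 0, 1, 2: interaction OR 0.29 per year.
- Time numeric 1, 2: interaction OR 0.28 per year.
- Time centred at mid-study: interaction OR 1.0, both arms fitted at 36.9%. The gap is missed.
- Time as a three-level category: the design matrix has rank 6 of 6 and so equals the saturated model. Each group-by-time term is then the arm difference within that year.

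**Step 3: simulation at the projected size.** 24 v 26 cases, constant 58.3% v 15.4%, likelihood-ratio test of the interaction at 0.05. The figures are proportions falsely significant; ranges are across separate runs.

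| Model | Listed terms | Arm added |
|---|---|---|
| Ward random intercept, continuous time from launch | 51–56% | 7% |
| Ward random intercept, year 1/2 | 67% | 8% |
| No ward effect, continuous time from launch | 82–84% | 7–9% |
| No ward effect, year 1/2 | 84–90% | 5–8% |

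Other settings without the ward effect: year coded 0/1 gives 64%, and centred time 6–8%. With two yearly categories, a joint test of the group-by-time terms is significant in 87% of trials, against 8% for the proper interaction test with arm in the model. A smaller constant gap of 58% v 35% gives 35%, or 21% with ward intercepts.

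**Precision.** The ward-intercept figures rest on 250 to 300 trials each. The standard error is √(0.51 × 0.49/250) = 3.2 points at the lower end and √(0.667 × 0.333/273) = 2.9 points at the upper end. They should be read as roughly half to two thirds.

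**Assumptions.** Case times are spread evenly over two years and there is no true ward variance. Cases were shared across intervention wards either equally or by screening population (2926:998:1876). In the runs that recorded failed fits, about 1–9% of datasets were dropped for that reason.

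**The case against.** The strongest reply is that the sentence is garbled, not wrong. Time appears twice and a comma splits the interaction, so one mention may have been meant as allocated group. The source is also a condensed article. That is plausible, but the terms are stated, and an analyst who follows them fits the wrong model. Settling the point after the data are seen could change the conclusion on trend.

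Four stronger readings are tempting, and the documents do not support them.

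- **That the trial has no test of the arm effect on its primary outcome.** It has one: the overall late-stage comparison by Chi-square or Fisher's exact test, on which the 23 cases per arm were sized. The yearly comparisons also stand outside the model. The regression is additional.
- **That the model always yields a false trend.** This holds for numeric time counted from launch. The surrounding text speaks of years, and with yearly categories the listed terms estimate an arm effect in each year without bias. The error would then lie in reading those terms as a trend test.
- **That the first-year 7/12 v 2/13 proves the LGAs differed at launch.** Those cases accrued after the programme began. The protocol expects late-stage numbers to be high at the outset and to fall in the intervention arm. The data show only that equality at launch is not assured and should not be built into the model.
- **That adding arm isolates the programme effect.** With one LGA per arm, the arm coefficient also carries any fixed difference between the LGAs.

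It is also fair to say that the 82–87% range omits the planned ward effect. The 51–67% range is the one that describes the stated model.

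**Conclusion.** Wrong as written, within a supplementary analysis. If time is numeric and counted from study start, the listed terms impose equal stage IV odds at launch and convert a constant gap into an apparent difference in trend. At the projected case numbers and a constant 58.3% v 15.4%, this occurs in about 51–67% of trials with the planned ward intercept, where a correctly specified interaction test gives about 5–9%. The size depends on the true gap and on the coding of time, which the protocol does not state. Centring hides the gap, and yearly categories change what the terms mean. The planned Chi-square or Fisher comparison and the yearly comparisons are sound in this respect.

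**What to change.** Specify the model on confirmed cases as late-stage ~ arm + time + arm:time, with a random intercept for ward. State whether time is continuous or a yearly category, its unit and its origin. Name arm:time as the trend contrast. Name the arm coefficient, at the stated time origin, as the between-LGA difference, and add that with one LGA per arm it cannot be separated from a fixed LGA difference.

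This is one sentence, with no operational cost. The price is apparent power that the trend test never validly had. In simulations without the ward effect, a real fall in the intervention arm from 58% to 5% is detected in 84% of trials with the listed terms and in 31% with arm included. The 84% is no gain, because in the same setting a constant gap is flagged in 82%.
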